| --- |

| **7. PROGRESS REPORT/PRELIMINARY STUDIES** |
| --- |

| Data collection from the first phase of the study (involving Tijuana and Ciudad Juárez) is now complete. A total of 900 female sex workers (FSWs) 18 or older who reported having unprotected sex with at least one client within the previous month were recruited, 450 in Tijuana and 450 in Ciudad Juarez, Mexico. After a baseline assessment, participants were randomly assigned to either: (1) Proyecto Comparte Sexo Mas Seguro (“Share Safer Sex”), a theory-based counseling intervention to increase the use of condoms; or (2) time-equivalent voluntary HIV counseling and testing. FSWs in the intervention and comparison conditions showed no significant differences in baseline demographic characteristics, sexual risk behaviors, or HIV serostatus, which indicates that randomization was successful. A total of 171 (19%) participants were lost to followup, which is a low attrition rate for a study of this kind. Data are currently being analyzed to determine the efficacy of the Comparte Sexo Más Seguro program as compared to the time-equivalent counseling program. As reported last year,10a substantial differences were found in certain psychosocial, disease-prevalence, and drug-use variables between the Tijuana and Juárez cohorts, which could provide the basis for a future tailoring of the subject intervention to local conditions. That article, in turn, formed the basis for a poster presentation at the 2006 International AIDS Conference in Toronto.10b Meanwhile, members of our research team have written additional studies of the data obtained in the first phase. [name] authored an article examining the impact of price and workplace on female sex worker condom use in Tijuana and Ciudad Juarez.10c Also at the 2006 International AIDS Conference in Toronto, a student trainee presented preliminary results of her study of the relationship between workplace type (e.g., brothel vs. street) and sexual risk behavior among FSWs in Tijuana and Ciudad Juárez.10d  The second phase of the study, to be carried out in Nuevo Leon and Matamoros in Tamaulipas State, is well under way. All staff have been recruited and trained, and 40 new participants (of a projected total of 900 for these two sites) have been recruited.  There are no site monitoring reports, audits or other reviews to report since the last IRB approval in October, 2005. |
| --- |

| **8. RESEARCH DESIGN AND METHODS** |
| --- |

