| This four-city study uses a pre-test, post-test, random assignment, In each treatment city, 450 female sex workers who have had unprotected sex with a client at least once during the previous four weeks will participate in baseline assessment; then randomly assigned to either Condition A (Share Safer Sex counseling session) or Condition B (the CDC’s safer sex program); and finally a six-month followup assessment. Concurrently, another 450 FSWs the second city will participate in the same programs. As noted above, we have completed our data-collection work in Tijuana and Ciudad Juarez, and we have moved on to the second pair of cities (i.e., Nuevo Laredo and Matamoros). As in the first phase of the study, randomization to condition A or B will be performed using a fixed, computer generated randomization scheme to ensure approximately equal allocation to each study condition. In order to reduce potential contamination between the two counseling conditions, participants will be randomly blocked by condition weekly.  Condition A: Within each of the cities, 225 FSWs, a random selection of the 450 FSWs in each city, who meet eligibility criteria and complete a baseline 60-90 minute sexual risk appraisal interview, will participate in the 45-minute Share Safer Sex counseling session. This one on one intervention utilizes motivational interviewing techniques and principles of SCT/TRA to address the context of unsafe sex and condom use with clients (see more detailed description of interventions below). A total of 900 FSWs will receive Share Safer Sex counseling in four cities (225/city).  Condition B: Within each of the cities, 225 FSWs, a random selection of the 450 FSWs in each city, who meet eligibility criteria and complete a baseline 60-90 minute sexual risk appraisal interview, will participate in the 45-minute, one on one, CDC-based “standard counseling” session that offers a personal risk assessment and strategies for reducing personal risk. A total of 900 FSWs will receive the CDC program in the four cities (225/city).  Description of Four Study Cities. Each of the four participating study cities has a large number of female sex workers, ranging from 2,200 in Nuevo Laredo to 6,500 in Tijuana and Ciudad Juarez11. The majority of the sex workers receive monthly medical care at the municipal clinic in their city. The large number of sex workers in each city, will help to ensure the successful recruitment of 450 FSWs in each treatment and comparison city. Apart from the pilot study that was conducted by our research team in Tijuana, none of the participating cities has in the past or present offered sexual risk reduction counseling programs for FSWs. Below, we provide a brief description of each study city, and indicate the estimated number of female sex workers. We begin with a description of the border city of Tijuana, Mexico. Tijuana is the largest port of entry to the U.S, and the second largest city along the US-Mexico Border (i.e., 1,212,232 residents). In 1999, there were 18.7 million crossings between Tijuana and San Diego, CA12. The main industry in Tijuana is maquiladora assembly plants. Tourism is the second largest industry in Tijuana. Main attractions include bullfights, nightclubs, and bars. Health officials in Tijuana estimate that there are approximately 6,500 female sex workers in this border city11. The largest Mexican border city is Ciudad Juarez. Ciudad Juarez is the also largest city in the state of Chihuahua. It has a population of 1,217,818 and is the port of entry from the U.S. city of El Paso, Texas. In 1999, there were 20.9 million border crossings at this location12. The main industry in Cuidad Juarez is maquiladora assembly plants. It is estimated that there 6,500 female sex workers in the city of Ciudad Juarez11. Nuevo Laredo is the forth largest border city in Mexico, with a population of approximately 750,000. It shares a border with Laredo Texas It is the main gateway to the U.S. for the trucking industry with approximately 80% of all trucks entering the U.S. from Mexico passing through this city.. In addition to trucking, the main industries are agriculture and maquiladora assembly plants. Mexicali shares a border with the U.S. city of Calexico/El Centro. Popular tourist attractions include bullfights, nightclubs, and bars. It is estimated that there are 3,000 female sex workers in the city of Nuevo Laredo. Nuevo Laredo and Matamoros are similarly sized border cities. Matamoros has 416,428 residents is the second largest city in the State of Tamaulipas. Matamoros shares a border with Brownsville, TX. Matamoros is the main port of entry for the U.S. population from Texas and New Mexico. In 1999, there were 7.1 million border crossings at this location12. The main industries in Matamoros include agriculture, maquiladoras, and tourism. It is estimated that there are 2,200 female sex workers in the city of Matamoros11.  Description of Study Sites: In the proposed study, all interviews and counseling sessions will be conducted at either Government-operated Municipal Medical Clinics, NGOs who specialize in FSWs, or clinics set up by our staff. All four participating cities have clinics located downtown, and within walking distance for the majority of FSWs where treatment referrals will be made if necessary. Each clinic is equipped with an OBGYN examination room, and several additional exam rooms. Women are seen on a first-come, first-serve basis. They register at a desk at the entrance and await their turn. Although some of these clinics are funded by the local municipal governments, the women are expected to pay $40 US for the cost of their medical visit and lab work. Lab work is performed by clinic-affiliated laboratories. Because the municipal clinics are directly responsible for STD/HIV surveillance, they provide clinical services to active sex workers, both male and female. Typically, municipal clinics are staffed with three physicians (including an OBGYN), and three clinical nurses. A social worker and psychologist are also available to provide medical and social services to FSWs. In order to receive or renew a work permit, FSWs are required to undergo clinical examination at a municipal clinic. Only municipal clinics have government accreditation to issue work permits to FSWs. In order to enrich our sample we also recruit women from bars and other venues who are not seeking work permit. These women are brought to the study clinic for interviews and exams.  Recruitment Procedure: Recruitment is conducted at municipal clinics, NGOs, or using street outreach in each participating city. Recruitment of FSWs at the Municipal Clinic in Tijuana (SMM), and street outreach was highly successful; thus, this general approach to recruitment will be utilized in all clinics in the proposed study. Other methods of outreach are standard in the field. The key component to gaining full access to the women was to “cultivate” relationships with the secretaries, receptionists, and nurses who have great influence on the dynamics of SMM. The research staff was very respectful and valued their opinion on recruitment issues. Women were approached after they signed up for their appointment and offered participation. The refusal rate was very low (i.e., 2.5%).  Study Procedure: Recruitment of FSWs into this study will utilize a lagged design. In each treatment city, we will recruit, counsel, and conduct followup interviews with approximately 450 FSWs over a 30-month period. (There will be two 30-month waves of data collection to coincide with our two pairs of cities). Concurrently, 450 FSWs in each city will participate in baseline assessment, counseling, and six-month followup evaluation. FSWs will be interviewed alone by clinic staff who are the same gender. The staff in each treatment city will be comprised of one female interviewer and one counselor both of whom will have had prior experience working at the designated site. In our pilot work, we found that familiarity with the interviewer and counseling staff enhanced the candidness of FSWs responses. Each recruitment site will also be staffed by a site manager and clinical coordinator.  Description Of Assessment Procedure. All assessments will take place in the clinic. Participants will be interviewed face-to-face in privacy by our staff. Because of low reading level, all materials will be administered verbally. The assessment battery requires approximately 60 to 90 minutes to complete.  Study Eligibility: Inclusion criteria. Participants must be women (at least 18 years old) who self-identify as a “female sex worker” and report having had unprotected vaginal, oral, or anal sex with a client at least once during the previous four weeks. Exclusion criteria include: (1) consistent use of condoms/dental dam for vaginal, oral and anal sex with all clients during the previous two weeks; and (2) employed as a sex worker for less than 4 weeks (i.e., to match our 4-week period of recall); (3) under 18 years of age. The latter exclusion criterion was imposed because it is illegal for women under the age of 18 to engage in prostitution in Mexico. Accordingly, FSWs under the age of 18 would not attend the municipal clinic for health care and therefore would not be recruitable. We considered allowing males who identified as FSWs into this study; however, in our pilot study less than 2% of clients at the Municipal Clinic were men who identified at FSWs. In the proposed study, we anticipate an insufficient number of males who identify as FSWs to make their data usable; hence, they have been excluded from study participation. Also, a study of male sex workers would require different recruitment strategies and a targeted intervention to reflect the sexual behaviors and sexual milieus of this population.  FSWs who report intravenous drug use will be included in our study. While our pilot data indicate a low frequency of intravenous drug use (IDU) among FSWs in Tijuana, which is consistent with other studies of Mexican FSWs, we want our sample to be inclusive. Our intervention counseling does not address injection drug use; however, FSWs who report that they have ever injected drugs or vitamins will be provided with written materials (Spanish) on safer injection practices. For those who are illiterate, the written materials provide detailed graphic depictions of how to clean a needle. Also, FSWs who do not have work permits will be allowed to participate in this study.  Definitions of safer sex. We define sexual risk behavior as unprotected insertive or receptive sex (vaginal, oral, or anal). Our definition includes unprotected oral sex. The U.S. Surgeon General’s report states that “getting semen, vaginal secretions, or blood from an infected person into your mouth puts you at risk of HIV infection”13. Although the risk of HIV infection from oral sex is lower than from VA sex, sores or cuts anywhere in the mouth make oral sex more risky13. Safer sex practices are defined as the use of condoms, or the practice of non-penetrative sex (e.g., manual sex). DiClemente and Peterson14 argue that most adults will fail to adopt sexual abstinence as a prevention strategy, thus, appropriate and consistent use of condoms is the most effective method for reducing HIV/STD exposure. In this study, we promote condom use and non-penetrative sex as the best HIV/STD prevention methods. Also, we promote harm reduction strategies, which have lower levels of risk (e.g., when engaging in oral sex have client ejaculate outside of mouth).  Training Procedure: Interviewers and counselors from all sites have received a two-day training led by the UC Davis training team. This program includes the following modules: (1) an overview of the proposed research project, including an overview of data on the sexual health of women in Mexico;(2) research ethics and treatment of human subjects; (3) an overview of potential population based cultural biases and ethnographic research methods, (4) appropriate interview methods, (5) cultural sensitivity as it impacts sexworkers in Mexico, (6) the “culture” of prostitution in Mexico, (7) public health issues impacting sex workers in Mexico, (7) identifying and handling co-morbidity issues that may surface during interviewing and counseling sexworkers , (8) issues in prevention; (9) appropriate intervention strategies; (10) safety considerations for interviewers and counselors, and (11) key points in addressing self-esteem issues with sexworkers. Self-assessment by the participants resulted in an overall high assessment of the training workshop. All training was conducted in Spanish and included a Spanish-language handbook with key points covered during the training. Counselor training procedures were adapted from the earlier pilot study and will continue to be adhered toin the remaining two study cities.  Subject Accrual and Attrition: At the end of the five-year study period, we expect to have evaluated a total of 1,800 FSWs. The first wave of the study, which recruited 900 FSWs in Tijuana and Ciudad Juárez, took about 30 months to complete, and we expect the second phase (in Matamoros and Nuevo Laredo) to be similar. Staff in each city will recruit, assess, and counsel 450 FSWs (for a total of 900), and the same research procedure will be followed.  The first wave of the study showed a retention rate of 81%, which was approximately what we expected based on the rate for the pilot study in Tijuana, which was 79%.  Research Incentives. In order to provide an incentive for participation, we propose to continue paying $30.00 per visit. We will also continue to pay for STD/HIV laboratory tests ($40.00 U.S. per visit). All participants, whether in the treatment or comparison group, will receive approximately 100 condoms and some sexual lubricant. These incentives are modest enough to be non-coercive but substantial enough to encourage complete participation. The laboratory tests serve two purposes: they offer valuable health information to all participants, and they provide objective outcome data for the study.  Notification of Test Results. Laboratory test results will be given to the FSWs by Clinic Staff. When positive test results are obtained, standard notification, counseling, and treatment will be provided by the clinic.  Limitation of Study Design. There are at least two potential problems associated with our study design. The first is the possibility of non-random attrition. It is possible that women who are infected with an STD/HIV will be less likely to come back to the clinic since they may lose their health card/work permit. We argue that this is unlikely since there are few clinics available, and we will pay for clinic visits and laboratory tests. The second potential problem is that randomization of cities could lead to problems such as secular trends affecting our results. This was an issue that was vigorously debated by our research team; in the final analysis, the problems with contamination within single clinics were felt to override the potential problems with our proposed design. Our teams in each of the comparison cities will monitor changes in the clinics and changes in health policy that might affect our results. Stigmatization toward FSWs. At the simplest level, we need to beware of negative labeling that might lead to discrimination against participants. We will protect the confidentiality of our participants to the full extent allowed by U.S. law, including an NIH Certificate of Confidentiality. On another level, stigmatization could impede our efforts to change that most personal of all behaviors, i.e., sexual behavior. Our counselors will be non-judgmental; they will respect the participant’s individuality and take into account the emotions and personal values associated with sexual behaviors; and they will empower participants with the tools and skills they need to effect behavior change. DESCRIPTION OF PROYECTO COMPARTE SEXO MAS SEGURO: The development of intervention materials relied heavily upon our pilot work conducted in Tijuana, Mexico. It also borrowed from our experience conducting sexual risk reduction interventions in the U.S. In the proposed study, clinic-based health care staff are trained to deliver a sexual risk reduction intervention to FSWs. The content of our counseling sessions is tailored to the needs, values, beliefs, and behaviors of our target population. Our protocol takes into account gender differences in counseling issues, with special consideration given to the ecological validity of our intervention for Latinas. It combines principles of motivational interviewing, social cognitive theory, and the theory of reasoned action. To this end, the counselor asks questions about the participant’s condom use with clients, including her perceived need to change, perceived possibility of change, self-efficacy for change, and stated intentions to change. The counselor works with the participant to increase her awareness of current unsafe behaviors and associated risks (e.g., HIV, STDs, pregnancy). Motivational interviewing techniques (e.g., key questions, reflective listening, summarization, affirmation) are used to elicit information on the participant’s current situation and motivations. The goal is to help the FSW to see her situation clearly and accurately. Helping the individual to understand motivations that underlie her current unsafe behavior with clients is a prerequisite to changing her behavior18. In our pilot work, we learned that financial gain was the primary motivation for not using condoms with a client. It was not uncommon for FSWs to double their income if they were willing to have unprotected sex. Another common motivation for not using condoms focused on the type of client. Condom use was considered unnecessary if the client was elderly (“I’m not afraid of infection or pregnancy with him”) or a long-term client (“I like him and I trust him”). Other motivations underlying unsafe sex with clients included the lack of intimacy, discomfort, and bad taste associated with condoms. As the counselor and participant discuss these underlying motivations, the participant gains insight into her own behavior and she begins to build motivation for change. The information that emerges in the counseling session also provides the counselor with valuable information on the FSW’s values, expectancies, sense of self, and social/work context -- all of which influence motivation for change. Once awareness of the problem is achieved, the counselor will help the participant discover and understand her motivation for change. This is accomplished by spending time eliciting self-motivated reasons for change and enhancing the participant’s self-efficacy for change. In our pilot work, FSWs offered a plethora of self-motivational statements in relation to condom use with clients. FSWs motivations for using condoms with clients included the following: to avoid diseases (HIV & other STDS); to avoid pregnancy; to stay alive; to feel clean; to avoid direct contact with clients; to avoid getting sick again; to feel good about oneself; to avoid losing one’s job; to stay healthy for loved ones (family and children), to protect the client; to enjoy sex more; and to save time between clients. Counselors use the “decisional balance” approach18 to help the participant realize that, in most cases, reasons for using condoms with clients strongly outweigh reasons for not using condoms. Once the balance begins to shift in favor of positive change, the next step is to help the participant develop a plan of action that best suits her personal situation. The counselor asks about barriers to condom use. Barriers for female sex workers may include the threat of physical assault or death, rape, loss of clients, and loss of income. The counselor works with the participant to problem-solve these barriers. The counselor also offers information and suggestions on how to change behavior, and illustrates positive outcomes. The participant is actively involved in problem-solving and is encouraged to come up with solutions. The participant is presented with a menu of options. For example, the counselor presents a variety of safer sex options ranging from the use of male and female condoms for vaginal sex, to a variety of harm reduction strategies such as offering the client unprotected oral sex instead of unprotected vaginal sex. According to both motivational interviewing and social cognitive theory, belief in one’s ability to bring about change is an important motivator of change. It is very important that the participant attribute success to herself. The counselor also helps the participant to define achievable goals (e.g., always use a condom for vaginal sex with clients). Once the participant has defined goals and arrived at a plan of action, the participant and counselor engage in problem-solving exercises. Alternate choices of behavior and alternative strategies for dealing with the situation are discussed. Rewarding the participant with positive feedback helps to enhance self-efficacy. The counselor aims to strengthen the FSWs commitment to using condoms by exploring ways to make condom use exciting and erotic for the client. The counselor and participant also practice putting a condom on and taking it off a 5odríg penis model while discussing how to keep the man erect (e.g., licking penis shaft or testicles). The counselor and participant also discuss the participant’s successes, and the counselor makes suggestions for improvement if necessary. It was readily apparent in our pilot study that many FSWs did not know how to use a condom properly. The majority of women reported previous experiences with clients where a condom broke, tore, or stayed inside the vagina upon termination of the sexual act. For example, a common practice among sex workers in Tijuana is to use two condoms on the client’s penis. This practice resulted in condoms slipping off during sex or getting lodged in the vagina. Also, the popularity of long fingernails among FSWs in Tijuana contributed to frequent experiences with torn condoms. Condom failure also occurred as the result of using body lotions and vaginal medications as lubricant. Overall, FSWs in the pilot study expressed much gratitude for the condom demonstration exercise and the information regarding proper condom use. Demonstration and practice exercises are designed to enhance the participant’s attitudes, self efficacy, positive outcome expectancies, and intentions to use a condom. Creating a positive, supportive atmosphere that makes the use of condoms appealing to the individual is conducive to behavior change. The counseling session takes 40 to 45 minutes. The order and approximate duration of intervention activities are presented in the counselor training manual. They include: Assessing Readiness for Change (5-7 minutes); Decisional Balance Exercise (3 minutes); Building Motivation for Change (10 minutes); Identification of Problem & Problem-solving Exercise (7-10 minutes); and Knowledge & Skill-building Exercises (10 minutes).  DESCRIPTION OF STANDARD COUNSELING SESSION: The comparison condition for this research utilizes a modified version of the Centers for Disease Control’s revised guidelines for HIV counseling, testing, and referral19 and materials from Mexico’s National Center for AIDS Studies (CENSIDA). The face-to-face counseling session takes about 45 minutes. The focus of the counseling session is upon personal risk assessment and strategies for reducing personal risk. During the personal risk assessment component, the counselor helps the participant to identify, understand, and acknowledge behaviors and circumstances that put her at risk for contracting HIV and other STDs. The counselor also explores the participant’s previous attempts to reduce personal risk, and provides positive reinforcement for positive steps already taken. The counselor also helps the participant to set small, achievable risk-reduction goals and offers concrete suggestions for achieving personal goals. Basic educational information (e.g., HIV/STD transmission modes) is provided if the individual’s level of knowledge is low; however, the primary focus is on the discussion of transmission risk associated with specific behaviors or activities that are relevant to the participant’s personal risk. Lower risk alternatives to risk behavior are promoted (e.g., although oral sex is not risk-free, it is associated with lower risk for HIV infection as compared to unprotected vaginal sex).  MEASURES. All measures have been translated into Spanish and back-translated into English by a bilingual team of Latino/a researchers. In addition, all measured have been reviewed for cultural appropriateness by one of our collaborators, [name], Director of the Mexican Psychiatric Institute in Mexico City.  BEHAVIORAL OUTCOMES. O’Leary et al.20 discuss the difficulties in selecting behavioral outcomes in HIV/STD prevention research; every measure has strengths and weaknesses. Behavioral outcomes in this study will include: frequency of unprotected vaginal, oral, and anal sex with clients and spouse/steady partner; protected sex ratio (number of protected sex acts divided by total number of acts); number of clients; number and type of other sex partners (non-clients); number of partners who inject; number and type of STDs; and incidence of HIV/AIDS.  Condom Use: We will assess condom use with clients and spouse/steady partner. FSWs will report the number of times they engaged in vaginal, oral, and anal sex without a condom (or dental dam) with clients and their spouse/steady partner during the past two weeks.  HIV Testing and Sexually Transmitted Diseases. In addition, participants will receive free screenings for HIV, syphilis, gonorrhea and Chlamydia, based on a blood sample and vaginal swab. Pre-test counseling will also be provided, which will include basic information on how these infections can be transmitted and which preventive behaviors can reduce risks. A trained phlebotomist will obtain a venous blood sample from each participant to permit antibody testing for HIV and syphilis. In the case of HIV, we will use a rapid antibody test which is considered highly sensitive and specific (called “Determine”, manufactured by Abbott). The test device, which resembles a dipstick, is then inserted into the vial. In as little as 20 minutes, the test device will indicate if HIV-1 antibodies are present by displaying two reddish-purple lines in a small window on the device. Depending on the results of the rapid HIV test, each participant will receive immediate post-test counseling before leaving the study site. In the event that a rapid test for HIV is positive, a second blood draw will occur immediately into a 10 cc CPT tube, which is necessary to extract viral RNA for genotypic analysis. We will also use this specimen confirm any positive results of the rapid HIV test using ELISA and confirmatory Western Blot, as a further quality assurance measure. As a result, the amount of blood for HIV-negative participants (approx. 2 tablespoons) will be somewhat less than for HIV-positive persons (4 tablespoons), but not significantly so. Persons testing HIV-positive on the rapid HIV test will be counseled that their test was positive and that, while it is highly likely that they are infected with the virus, we ask them to return in one month for confirmation based on the standard ELISA and Western blot test. In accordance with CDC guidelines, counseling includes education about risk reduction (e.g. abstaining from injection or sexual contact, or using sterile syringes or condoms).  The remainder of the blood sample will be shipped to a laboratory in San Diego County where an aliquot will be tested for syphilis antibody, and HIV antibody confirmation will be arranged for through the state laboratory in the case of a positive specimen. The second aliquot will be stored at -80C for future testing of STDs and blood borne pathogens including syphilis. Women will also be asked to provide two vaginal swabs which will also be shipped to the same laboratory. One swab will be prepared for ligase chain reaction to amplify genetic material for gonorrhea and Chlamydia. The other swab will be stored at -80C for future testing of STDs, if funding permits.  All women will be asked to return for test results within one month, at which time post-test counseling will occur. In the event that a participant tests positive for HIV or an STI, feedback will be provided by regular clinic staff (either a physician or psychologist) who are trained to provide this feedback in a sensitive manner in order to reduce psychological distress. Referrals to the Municipal Clinic in that city will be made where regular HIV treatment is provided.  Women will be compensated $30 U.S. per visit for their time. Although we are quite confident that these incentives will be effective, we will also utilize cohort maintenance procedures that were successfully implemented in our pilot study in Tijuana. These long-established principles which were delineated by Robins15, Boice16, and Showstack et al.17, have been modified for use with FSWs. Below, we describe some basic cohort maintenance procedures that were successful in our pilot study. Retention at six-month followup in the pilot study was 79 percent (21% attrition). In the proposed study, reasons for study attrition will be recorded for all participants, if known. Other STDs will be assessed by self-report (e.g., 6odríguez, syphilis). Self-report of STDs will be validated by a review of patient charts at each clinic. The review of patient charts will be conducted by the clinical coordinator at each site.  MECHANISMS OF CHANGE VARIABLES.  Knowledge: Our new measure of knowledge21 consists of 18 items, which assess the participant’s awareness of the importance of condom use with respect to HIV/STD prevention (e.g., “People who have been infected HIV quickly show serious signs of being infected”; “A person will not get HIV if she or he is taking antibiotics”). Response categories are True (1) or False (0). Internal consistency alphas range from .75 to .89, and test-retest reliability range from .76 to .94.  Self-Efficacy: Our 5-item measure of self-efficacy asks participants to indicate the extent to which they are able to use a condom properly with clients. Responses are coded on a 4-point scale (1=Strongly Disagree to 4=Strongly Agree). The alpha for this scale is .85.22  Outcome Expectancies: Participants respond to three items using a 4-point scale ranging from 1 (Strongly Disagree) to 4 (Strongly Agree). An example of a positive outcome expectancies is: “I believe that condoms will protect me from getting HIV). The alpha for this scale is .79.22  Attitudes toward AIDS Preventive Acts: Two items will be used to measure attitudes toward AIDS preventive acts23. “My not having (vaginal/oral/anal) intercourse with my clients during the next two months would be: very good (5), somewhat good (4), neither good nor bad (3), somewhat bad (2), and very bad (1)”; and “My always using condoms for (vaginal/oral/anal) intercourse with all my clients during the next two months would be (response categories noted above). Each item will be asked separately in relation to vaginal, oral, and anal sex. The alpha for this scale is .79.  Intentions to Engage in AIDS Preventive Behavior: Intentions will be captured by two items: 1) I intend not to have (vaginal/oral/anal) intercourse with my clients during the next two months; and 2) I intend to always use condoms for (vaginal/oral/anal) intercourse with all my clients during the next two months. Response categories are measured on a 5-point scale (5= very true; 4=somewhat true; 3=neither true nor untrue; 2=somewhat untrue; 1=very untrue)23. Each item will be asked separately in relation to vaginal, oral, and anal sex. The alpha for this scale is .89.  Perceived Social Norms: Perceived expectations for AIDS prevention behavior will be measured by two items: 1) Most people in my line of work think that I should not have vaginal intercourse with my clients during the next two months; and 2) Most people in my line of work think that I should always use condoms for vaginal intercourse with all my clients during the next two months. Response categories range from 1 (very untrue) to 5 (very true)23. These two items are repeated for oral sex and anal sex with clients. The alpha for this scale is .96.  CONTEXTUAL FACTORS  Working Conditions is a multidimensional construct with multiple indicators that include work site (e.g., brothel, street, bar), type of sex worker (e.g., dance hostess, street worker), degree of protection from drunk or aggressive clients, nature of relationship with pimp (if applicable), availability of condoms, earnings, type of sexual services performed, control over selection of clients. An overall rating of work conditions is also provided by the participant (1=very unfavorable) to (5= very favorable).  Drug and Alcohol Use will be measured by a 5-item scale developed by Temoshok & Nannis24. FSWs will be asked to report their use of alcohol, marijuana, cocaine, heroin, hallucinogens, and ecstasy preceding and during sex with clients for the previous two months. They will also be asked about their general use of alcohol and drugs. Frequency and amount consumed will be recorded at each assessment.  Victimization and Trauma will be measured by four items derived from the family/social relationships section of the Addiction Severity Index (ASI-F). The section concerning abusive relationships contains questions about past and present episodes of physical, emotional, and sexual abuse. Participants will be asked four questions in relation to male clients, pimp, and spouse/steady sex partner. Sample items include: “In the past 30 days, did any of your (male clients) abuse you emotionally (make you feel bad through harsh words, humiliation, manipulation; and “In the past 30 days did any of your (male clients) abuse you sexually (rape, forced sexual advances, or non-consensual sex acts)”. The ASI has good test-retest reliability (>.80), as well as concurrent and discriminant validity25.  SOCIAL FACTORS  Social Support will be assessed using a modified version of the Schaefer, Coyne & Lazarus Inventory26. Three dimensions of support will be assessed in relation to safer sex: (1) satisfaction with emotional support; (2) satisfaction with informational support; and (3) network support. The participant is provided with a list of 16 network members. She then rates each person on five items that tap the person’s reliability, trustworthiness, caring, confidant qualities, and information provided in relation to safer sex. A 5-point response scale is utilized (1=not at all to 5=extremely). Satisfaction with emotional and informational support is averaged across all network members. Network size is defined by the total number of persons rated. Internal consistency reliability for the original scale is .95; test-retest reliability is .66.  Social Influence assesses the extent to which specific social network members engage in high risk behaviors. Participants are presented with three categories of individuals: other female sex workers (4 FSWs with whom you have the most contact or feel closest to); pimp; and husband/steady partner. For each of these six individuals, the participant is asked to rated the extent to which this person engages in the following behaviors: sex with clients without condoms (N/A for pimp and steady); sex with multiple partners without condoms (other than clients for FSWs); drug use before or during sex; alcohol use before or during sex; and intravenous drug use. Ratings are made on a 4-point scale ranging from 1 (not at all) to 4 (very often).  Life Experiences Survey is a self-report measure that rates the desirability of positive and negative life experiences that have occurred during the past six months27. Endorsement of an item indicates that an event has occurred. Participants will be presented with a list of events or life changes that are typically experienced in the general population. The original list of 47 events was reviewed by a panel of experts from the Universidad de Baja Mexico and modified to enhance cultural sensitivity. Three items were dropped. Three blank spaces permit the participant to report and rate the occurrence of other events that do not appear on the list. Desirable life experiences and undesirable life experiences are rated separately using a 5-point scale ranging from –2 (extremely negative) to +2 (extremely positive). A positive change score is calculated by summing the ratings for life events designated as positive by the participant. Similarly, a negative change score is computed by summing the ratings for negative events or experiences. The positive and negative change scores will be summed to create a total change score, which represents all change experienced during the past six months. The original LES has acceptable internal consistency reliability and test-retest reliability, ranging from .54 to .88.  INTRAPERSONAL FACTORS.  Depressed mood will be assessed using the Beck Depression Inventory28,29. This measure consists of 21 items, each having four graded statements pertaining to how the participant has been feeling during the past week. The statements within a question are ordered (0 to 3) to showing increasing depressive symptoms. Summary scores are calculated (range 0 to 63). The items of the BDI are clinically derived and have undergone extensive reliability and validation studies. Internal consistency assessments of reliability have been high (>.9).  Self-esteem will be assessed using the Rosenberg self-esteem scale30. Self-esteem is an element of self-concept that refers to the regard in which one holds oneself. It is conceived as a global construct, the assessment of which is not tied to a particular context. The self-esteem scale consists of eight items that are measured on a 4-point scale ranging from 1 (Strongly Disagree) to 4 (Strongly Agree). Sample items include: “I feel that I have a number of good qualities”; “I wish I could have more respect for myself”; and “On the whole, I am satisfied with myself”. The self-esteem scale has good test-retest reliability, as well as construct validity.  BACKGROUND CHARACTERISTICS  Financial Need will be assessed by five items that ask about the participant’s earning from sex work, earnings from other sources of work, number of people who are financial dependents, and the nature of relationship with financial dependents. An overall rating of financial need is also obtained from participants.  INTERVENTION IMPLEMENTATION ISSUES.  Quality Assurance. We will utilize two CDC-endorsed strategies31 for ensuring counselor adherence to the protocol: 1) Supervisor Observations. The clinical coordinator in each treatment-comparison city will observe each counselor in session with a participant once per week for a period of three weeks post-training. Corrective feedback will be provided. Thereafter, supervisor observations will be conducted once every three months; 2) Participant Evaluations. This method involves asking each FSW to complete a brief checklist that queries the content of her counseling session.  Strategies to minimize self-report bias in sex research. We will utilize multiple strategies for minimizing self-report bias32: (1) We will emphasize confidentiality by assuring anonymity through the use of ID numbers, and strict rules regarding confidentiality; (2) Project staff will provide FSWs with assurance of confidentiality and reinforce the importance of providing honest responses; (3) Project staff will give participants an opportunity to discuss concerns or fears before and after enrollment; (4) To encourage participant “openness”, our project staff will be open, non-judgmental, and have good rapport-building skills; and (5) Project staff will be individuals who have previously worked at the clinic so that they are familiar faces to the FSWs.  Data System. The data system to support the coordination of this project must acquire, store and provide access to data associated with our protocol from our participating sites. We will continue to use the data management system developed as part of our pilot study. This includes weekly transfer of hard copies of data (note that no data were lost in this process), and weekly feedback in order to maintain data quality.  Quality Control of Data. Our research group has devised procedures to minimize data loss. All data are delivered to and tracked by the data manager in San Diego. All items are entered into a computer database with entry screens developed in SPSS-DE. These screens require double entry for data verification. Data are maintained and backed up daily to prevent loss and to ensure full retrieval for analyses. Security is maintained through a password system. Our database contains no personally identifiable data, and participant records are identified only by a sequential study identifier.  DATA ANALYSIS. All data analysis will be conducted at the UCSD Coordinating Center. The first stage of analysis will involve tests for normality of distributions for each variable, with appropriate transformations as required. We propose to utilize two general data analytic strategies: 1) Analysis of variance techniques (i.e., repeated measures MANCOVA and group x time repeated measures ANCOVA and MANOVA); and 2) multiple regression. |

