| Recruitment Sources. Our remaining sample of 900 FSWs will be recruited through health clinics in Matamoros and Nuevo Laredo.  Participant Followup and Tracking. To enhance our understanding of the challenges associated with tracking a large cohort of FSWs in a third world country, [name] contacted a number of international researchers with expertise in this type of research in a range of countries including Thailand, Africa, Dominican Republic, Vietnam, India, and Latin America. All experts agreed that the best strategy for assuring optimal followup is to conduct the intervention in a health clinic setting because FSWs will return for health care services. Other important suggestions for ensuring good followup included subject payment for participation, a non-coercive approach, and easy access to the clinic for FSWs from their place of work/residence. Since the proposed study will be conducted in municipal health clinics we anticipate (and it was our experience in the pilot study) that the women will be motivated to return to the clinic on a monthly basis as required by law in order to keep their health card (working permit) current.  1. The participant will be advised in her first contact that she will be followed for a six-month period. She will be told that she is expected to attend two sessions (i.e., assessment/counseling and followup session), and undergo a free gynecological exam and blood test at each visit.  2. The participant will also be asked at her first visit to provide us with the name and telephone number of a contact (girlfriend, fellow worker, bar manager) whom we may contact if we have difficulty locating her at six month follow-up.  At her first visit, the participant will be given a card with the counselor’s name and telephone number. On the back of the card, the counselor will write the date of the next visit and the amount of the payment.  4. In our pilot work, we learned that some FSWs will consent to project staff leaving word “on the street” in the event that they cannot be located for their six-month followup visit.  5. The Municipal Clinic offers flexible hours, which makes it easier for FSWs to make it in for their visit.  6. It is critical when working with this population to develop strong bonds of trust and confidence. To this end, project staff in each research site will be carefully chosen for their sensitivity, discretion, and understanding of the needs of the target population.  7. FSWs will be advised at their first visit that if they move away, they will provided with a bus ticket or voucher to get them back to the clinic for their followup visit (if they have moved 100 miles or less from the clinic site). |

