| We judge that the benefits to participation in this project outweigh the riskswhich we will minimize wherever possible. Probably the most important risk associated with participation in this project is the risk that of a positive HIV test. This would result in the loss of the participant’s sex worker permit. However, on the positive side, the participant would be able to begin treatment and potentially prolong their life. In addition, the risk of unknowingly transmitting HIV to a client or other individual during a sexual contact would be averted. There are a number of other potential risks associated with participation in this project. These include the possibility that confidential information provided to research staff is inadvertently disclosed to someone outside this project. While this has never happened in the 22 years of the PI’s research experience, it is always possible. Therefore, we make every effort to guard against such happenings. This includes extensive training and monitoring of staff on issues of confidentiality, coding of data without names or other identifying data, and storage of data under the safest possible conditions. Other potential benefits for participation were outlined under Potential Benefits to participation. In our judgment, the potential benefits to the individual in the form of protecting their own health through learning about safer sex practices, information about their own health with associated treatment referrals, and the potential knowledge that this study will provide to science and public health officials outweigh the potential risks associated with participation in this project. |
| --- |

| **17. EXPENSE TO SUBJECT** |
| --- |

| None other than time taken. |
| --- |

| **18. PAYMENT FOR PARTICIPATION** |
| --- |

| Participants will be paid $30.00 per visit (maximum of two visits) for participation in this project. They will also be compensated indirectly in that their laboratory tests (i.e., for STD/HIV) will be paid for by this study, and they will be given approximately 100 condoms. |
| --- |

| **19. PRIVILEGES/CERTIFICATIONS AND LICENSES** |
| --- |

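### Stated follow-up of about 450 women per city conflicts with the protocol's own 81% retention, its case against infection-related attrition conflicts with its own text, and the named analyses by default leave out women who do not return

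*Protocol*

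**What the plan says.** **Follow-up numbers.** Section 8, Study Procedure, says of each city: "we will recruit, counsel, and conduct followup interviews with approximately 450 FSWs over a 30-month period". It then repeats the figure: "450 FSWs in each city will participate in baseline assessment, counseling, and six-month followup evaluation". Under Subject Accrual and Attrition it adds: "we expect to have evaluated a total of 1,800 FSWs". The same paragraphs give retention as 81% in the first wave and 79% in the pilot. Section 7 gives the count for the first wave: "A total of 171 (19%) participants were lost to followup".

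**Attrition related to infection.** Section 8, Limitation of Study Design, names non-random attrition as a potential problem: women with HIV or an STD may stay away because the permit is at stake. It then answers: "We argue that this is unlikely since there are few clinics available, and we will pay for clinic visits and laboratory tests". Three other places bear on that answer:

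- Section 16, on a positive HIV test: "This would result in the loss of the participant’s sex worker permit".
- Section 10, Participant Followup and Tracking, expects women to be "motivated to return to the clinic on a monthly basis as required by law in order to keep their health card".
- Section 8, Study Eligibility: "FSWs who do not have work permits will be allowed to participate in this study".

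**Analysis.** Section 8, Data Analysis, names two general strategies: analysis-of-variance techniques (repeated-measures MANCOVA, and group-by-time repeated-measures ANCOVA and MANOVA) and multiple regression. It states no analysis set and no rule for women without a six-month visit.

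**The concern.** Three things meet here.

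First, the number to be followed up equals the number enrolled, although the protocol knows from two sources that about a fifth are lost. A reader who takes 450 per city as the follow-up yield will expect more information than the trial can deliver.

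Second, the protocol identifies a plausible route to informative loss and sets it aside for reasons that its other sections undercut. The route matters because the listed outcomes include the number and type of STDs and the incidence of HIV. If women infected after randomisation stay away, the missing values are outcome events. If the counselling also prevents infection, more of those events would be missing in the comparison condition.

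Third, repeated-measures ANOVA and MANOVA with two time points, in their usual form, use only women seen at both visits. The multivariate forms also lose any woman missing one of the outcomes included. A comparison restricted in this way departs from the comparison of all randomised women in either of two cases: loss depends on the outcome differently in the two conditions, or the effect of counselling differs between those lost and those retained.

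**Working it through.** **1. Reproduce the stated loss.** Inputs: 900 recruited and 171 lost (section 7). 171/900 = 0.190, so retention is 729/900 = 0.810. This agrees with the 81% in section 8.

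**2. Expected follow-up.** Inputs: 450 enrolled per city, 225 per condition per city, four cities (section 8). Formula: enrolled × retention.

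| | Enrolled | At 81% | At 79% (pilot) |
|---|---|---|---|
| Per city | 450 | 364.5, about 365 | 355.5, about 356 |
| Per condition, four cities | 900 | 729 | 711 |
| Total | 1,800 | 1,458 | 1,422 |

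The stated 450 per city exceeds the expected number by 450 − 364.5 = 85.5, which is 19% of 450. The four-city totals assume that the second pair of cities retains women as the first pair did. The protocol's remark that the second phase should be similar concerns duration, not retention.

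**3. Cost in precision.** With 81% of women observed, standard errors grow by 1/√0.81 = 1.111, about 11%. The protocol gives no power calculation, so the following is an assumption. If 900 per condition gave 80% power at two-sided 0.05, power for the same effect would be about 71% with 729 per condition and 70% with 711. This is the price of attrition itself, and imputation would not recover most of it.

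**4. The argument against infection-related loss, set beside the rest of the protocol.**

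- Few clinics: section 8 says that only municipal clinics issue permits. Having few alternatives may therefore deter a woman who fears losing hers as easily as it brings her back.
- Paid visits and tests: section 8, Research Incentives, proposes to continue the $30 per visit and the paid laboratory tests. They were therefore already in place when 171 of 900 were lost.
- The permit as motive: section 10 relies on it. Section 16 says that a positive HIV test removes the permit. The rapid HIV result is given at the first visit, before the woman leaves, so it can influence whether she returns.
- Women without permits are enrolled, and others not seeking one are recruited from bars. The permit motive never applied to them.

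**5. How far selection could go (illustration).** Take baseline HIV prevalence p = 10%, the reported Tijuana figure in section 6, and 19% lost overall. Suppose infected women are lost R times as often; R is assumed, since the protocol gives no such figure. Loss among the uninfected is a = 0.19/(1 − p + pR), loss among the infected is Ra, and prevalence among those retained is p(1 − Ra)/0.81.

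- R = 1: 10.0%
- R = 1.5: 9.0%
- R = 2: a = 0.19/1.1 = 0.173, Ra = 0.345, prevalence 8.1%
- R = 3: 6.5%

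This shows a change in who is analysed, not a bias between conditions.

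**6. How far the estimate could move (illustration).** If loss is 19% in both conditions and counselling did nothing for the women lost, the completers' effect divided by the all-randomised effect is 1/0.81 = 1.235, an overstatement of about 23%. Both conditions are assumptions; neither is reported.

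**The case against.** **The analysis.** A reader might infer that the plan drops the 19% lost. The protocol does not say so. It names general strategies, including multiple regression, and fixes neither analysis set, covariates nor missing-data rule. Those commonly belong in a statistical analysis plan, which may settle them. This stands. What can be said is that the named ANOVA-type methods, used in their standard form, would leave these women out.

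**Informative loss.** A reader might infer that loss was related to infection, or that the retention scheme fails for infected women. Neither is shown. No section reports loss by infection status, permit status or condition. The permit is one of several devices: payment, free tests and examinations, a named contact, flexible hours, appointment cards and travel vouchers. Section 16 speaks of HIV, not every STD. The protocol itself lists non-random attrition as a limitation and will record reasons for loss where known. All of this stands, but it does not rescue the argument offered for calling such loss unlikely.

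**Bias.** Both conditions receive the same tests and payments, and first-wave HIV serostatus did not differ significantly between conditions at baseline. Loss tied to baseline infection and equal in both conditions mainly costs precision and generalisability. That stands too.

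**The 450.** It can be read as an enrolment target loosely worded, since 81% is openly reported and no sample-size calculation depends on it. The 1,800 evaluated may refer to baseline. The two statements that tie 450 per city to follow-up are harder to read that way.

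**Conclusion.** The point holds in three limited parts.

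- **Numbers.** The follow-up stated per city is not what the protocol's own retention delivers: about 365 at 81%, or 356 at 79%, against 450. The total would be about 1,458 (1,422) of 1,800 if all four cities behave alike. This is a misstatement of expected yield. It is not a failed sample-size calculation, because none is given.
- **Reasoning.** The dismissal of infection-related attrition is not supported as written. It conflicts with sections 10 and 16 and with the enrolment of women without permits, and the incentives it relies on coexisted with a 19% loss. The fault shown is in the argument; actual selective loss is not shown.
- **Method.** The named two-visit methods would by default exclude women who do not return. That departs from the all-randomised comparison only under the conditions set out above, and nothing shows that they were met. The 23% figure and the prevalence shifts are conditional illustrations, not estimates of error in this trial.

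The remedy is cheap, and first-wave data collection is already complete, so the changes are worth making.

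**What to change.** - Restate expected six-month follow-up as about 365 per city (356 at the pilot rate) and about 1,458 (1,422) in total. Say whether the 1,800 refers to baseline.
- Withdraw the statement that infection-related attrition is unlikely, or support it with a table of first-wave loss by baseline HIV/STI status and condition. Reconcile it with sections 10 and 16. With 40 of the second 900 recruited at the time of writing, the table would also inform follow-up in the remaining cities.
- Make the main analysis all women as randomised, using multiple imputation with condition, city, baseline outcome, baseline HIV/STI result and work site. Add permit status and recruitment venue only if they were recorded, since neither is among the listed measures.
- Add a delta-shift sensitivity analysis that makes the imputed values in the intervention condition progressively worse, and report how large a shift would change the conclusion.

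The cost is additional analysis work and a smaller stated follow-up number. The variables named for the main imputation model are already planned measurements. Imputation addresses possible bias and will not restore most of the precision lost.
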